### Missing data

We will automatically use multiple imputation if there are missing data, as we are aware that a small amount of missing data across multiple variables could result in a large number of incomplete cases and consequently limit the sample for a complete case analysis. We will conduct sensitivity analyses to investigate the effect of imputing these missing data on our results.^16–18^

### Multiple testing

We will account for multiple testing using permutation analysis where appropriate. A portion of the data included in this project was previously used in a study investigating the association of α-adrenoceptor blocking drugs and angiotensin-II receptor antagonists with AD and non-AD dementias.^19^ We anticipate the overlap between our study and this previous study to be around 4% for each of cohorts A and B and 9% for cohort C. The authors acknowledge that this might be a concern for multiple testing, however wish to highlight that the analyses conducted in this study will differ from those used before.

### Statistical methods

We will use four statistical approaches in our study—they are multivariable adjusted Cox regression, propensity matched regression, instrumental variable analysis and marginal structural models. We are committed to presenting the findings from all our analyses, irrespective of the direction of findings and will handle discrepancies between them by assessing the merits of each method in the given situation. If we discover large main effects of specific medications, we may investigate interactions between covariates and will seek to replicate any interactions in other large samples.

We will be using an intention to treat analysis in our primary analysis. The reasons for this are twofold. First, while there are theoretical statistical models for estimating the effects of treatment switching such as marginal structural models, these methods require the strong assumption that there are no unmeasured confounders. Second, to the best of our knowledge there are no instrumental variable methods for estimating the effects of treatment switching. We will investigate treatment switching using marginal structural models in a secondary analysis. All of the methods we will use for this study are summarised below.

#### Multivariable adjusted Cox regression

In our first analyses, a conventional observational analysis, we will estimate the HRs of incidence and survival using Cox proportional hazards models. Both analyses will use the actual prescriptions issued to the patients.^20^ We will report these associations adjusted for basic confounders (age and gender) and results adjusted for all measured covariates described previously. We will also perform tests of the proportional hazards assumption.

#### Propensity matched regression

In our second analysis, we will construct a sample of patients balanced on covariates and risk factors using a propensity score.^21–24^ We will construct propensity scores using a logistic regression of the actual treatment received on the covariates described above. Therefore, each participant's propensity score will be their conditional probability (odds) of receiving treatment or not (cohort types A and C), or receiving treatment versus control therapy (cohort type B). We will match each patient receiving one treatment to another patient receiving the control treatment with the closest propensity score on a ratio of 1:1 using a nearest neighbour algorithm with no replacement, and matching will be restricted to the common support region. Patients outside the common support region are those prescribed the treatment therapy with propensity scores higher than any patient prescribed the control treatment and vice versa. We will estimate odds ratios and HRs of the outcomes using the propensity score matched sample using logistic and Cox regressions.

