#### Cohort B

In this analysis, we will compare different drug subclasses that exist for a given treatment (listed in box 1). To do this, we will create a cohort of all patients who were prescribed a treatment and categorise them by the drug subclass they initially received. This will allow us to compare the outcomes for each of the resulting subgroups. For each treatment, we have defined the most frequently prescribed subclass as the control (indicated in box 1). In the primary analysis of this cohort, we will exclude patients initially prescribed the control subclass if they receive another subclass of the same treatment at the same time, however we do not expect this to be a common. We will explore the outcomes of individuals prescribed multiple subclasses, other than that specified above, in a sensitivity analysis.
Box 1The drug subclasses of interest for each treatment group with the control treatments indicatedTreatments for hypertensionBeta-adrenoceptor blocking drugs (control)Angiotensin-converting enzyme inhibitorsThiazides and related diureticsCalcium channel blockersLoop diureticsAlpha-adrenoceptor blocking drugsCentrally acting antihypertensive drugsAngiotensin-II receptor antagonistsVasodilator antihypertensive drugsPotassium-sparing diuretics and aldosterone antagonistsTreatments for hypercholesterolaemiaStatins (control)FibratesBile acid sequestrantsOmega-3 fatty acid compoundsEzetimibeNicotinic acid groupTreatments for type 2 diabetesBiguanides (control)SulphonylureasOther antidiabetic drugs

Follow-up for cohort B will start on the date of first eligible prescription as determined by a product code (see the treatment code lists in online supplementary files 1–3). Follow-up will end with the earliest of a relevant neurodegenerative disease diagnosis, death or censoring due to the end of registration at a CPRD general practice.

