### Study size

table 3 details the expected number of events for the event used to define the start of follow-up with the minimum sample size and detectable HR (α=0.05, β=0.80) for the Cox regression analysis of cohorts B and C. The minimum detectable HR is taken to be the detectable HR for the smallest exposed group tested against the control group. The minimum sample size is the sum of patients in the smallest exposed group and the control group. It is difficult to provide such details for cohort A due to its novel design that includes patients who are ‘at risk’ of the condition the treatment is used for. We can however consider the expected number of events listed for cohort B to be conservative estimates for the sample size of cohort A as all patients receiving treatment are included in cohort A by definition. This study will involve a large sample of data and has considerable power to detect even relatively small effects. Therefore, our statistical power will be more than adequate to test all of our proposed hypotheses, even under highly conservative Bonferroni corrections. Further details concerning the sample size and detectable HRs (α=0.05, β=0.80) for specific comparisons within cohorts B and C can be found in online supplementary files 6 and 7. Further details concerning the expected number of events, including at the drug subclass level, can be found in online supplementary file 8.

**Table 3 BMJOPEN2016012044TB3:** The expected number of events for the event used to define the start of follow-up presented with the minimum sample size and detectable HR (α=0.05, β=0.80) for the Cox regression analysis of cohorts B and C

Cohort	Start of follow-up	Expected number of events	Minimum sample size	Minimum detectable HR
B	Treatment for hypertension	1 018 519	269 808	0.968
	Treatment for hypercholesterolaemia	808 687	788 479	0.844
	Treatment for type 2 diabetes	200 800	158 775	0.943
C	Diagnosis of dementia (AD and NADD)	105 471	105 471	0.931
	Diagnosis of PD	20 686	20 686	0.870
	Diagnosis of ALS	2227	2227	0.600

AD, Alzheimer's disease; ALS, amyotrophic lateral sclerosis; NADD, Non-Alzheimer's disease dementias.

10.1136/bmjopen-2016-012044.supp6supplementary file

10.1136/bmjopen-2016-012044.supp7supplementary file

10.1136/bmjopen-2016-012044.supp8supplementary file

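### Propensity matching sets no limit on match distance, so where exposed and comparator groups are similar in size it keeps nearly everyone and leaves most of the measured imbalance in place

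*Protocol article*

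**What the plan says.** In the protocol article, under Propensity matched regression, the aim is stated first: "we will construct a sample of patients balanced on covariates and risk factors using a propensity score". The rule follows: "We will match each patient receiving one treatment to another patient receiving the control treatment". The control is chosen as the one "with the closest propensity score on a ratio of 1:1 using a nearest neighbour algorithm with no replacement, and matching will be restricted to the" region of common support. The section then defines who falls outside that region: those "prescribed the treatment therapy with propensity scores higher than any patient prescribed the control treatment and vice versa". The analysis of the matched set is given as: "We will estimate odds ratios and HRs of the outcomes using the propensity score matched sample using logistic and Cox regressions".

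No caliper, balance check or covariate adjustment after matching is mentioned. The Confounding section relies on comparing the four methods to bring uncontrolled confounding to light, and Statistical methods says that disagreements between them will be weighed on the merits of each method.

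**The concern.** Common support limits where on the score scale matching takes place. It does not limit how far apart two matched patients may be. When the region is set by the single most extreme patient in each group, tens of thousands of patients make it almost the whole score range. Matching without replacement then uses up the close controls, and the remaining exposed patients take whoever is left.

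At stake is the comparison of methods. If the matched HR keeps measured confounding that the Cox model has removed, the two will disagree because of the algorithm. That disagreement could be read as evidence about unmeasured confounding or about the drug.

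**Working it through.** **The plan's own figures.** The article gives no figure for the matching. The nearest is the minimum detectable HR in Table 3, which cannot be reproduced because neither event share nor exposed share is stated. It can be inverted with Schoenfeld's formula, reading the stated β=0.80 as power and the test as two-sided:

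P(event) × p(1−p) = (1.960 + 0.842)² / [N × (ln HR)²]

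For dementia, 7.85 / (105,471 × 0.00511) = 0.0146. That fits 3% exposed with 50% events, or 8% exposed with 20% events. Study size says this is the smallest exposed group, so it does not bound the other treatments in cohort C.

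**Why the ratio matters.** If both groups have n patients and all are matched without replacement, the matched set is the full sample, whichever patients are paired. Covariate means, and so the crude HR, do not change. More generally, at propensity score e the exposed and comparators occur in the ratio e : (1−e). Wherever e exceeds 0.5 there are too few close controls. Few patients are in that position when the exposed share is low, and many are when it is near or above one half.

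**Which comparisons are exposed to this (Table 3; control group: "we have defined the most frequently prescribed subclass as the control").**

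- Lipid drugs: 808,687 − 788,479 = 20,208 patients for the four subclasses other than statins and the smallest. The smallest is at most 20,208/4 = 5,052, so statins number at least 783,427. Against any one subclass that is at least 783,427/20,208 = 38.8 to 1. No problem.
- Diabetes: 200,800 − 158,775 = 42,025. If every patient falls in one of the three subclasses, the exposed share is at most 42,025/158,775 = 26.5%. Largely no problem.
- Hypertension ("Treatment for hypertension 1 018 519 269 808 0.968"): 1,018,519 − 269,808 = 748,711 for eight subclasses, a mean of 93,589. A subclass of that size would be 93,589/(93,589 + 269,808) = 25.8% of its pair. If five, four or three subclasses held the whole 748,711, shares would be 35.7%, 41.0% or 48.1%. That concentration is an assumption.
- Cohorts A and C: ratios not stated.

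**Simulation.** True HR 1; one measured normal confounder; common support by extremes; greedy 1:1 matching without replacement in random order; log-rank test at two-sided 5%. Weak confounding means log-odds of exposure 0.25 and outcome HR 1.2 per SD; moderate means 0.5 and 1.5; strong means 1.0 and 1.5. Confounder strength, event share and exposed share are all assumptions. The caliper is 0.2 SD of the logit.

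| N, events | Exposed | Confounding | SMD before → after | HR crude → matched | Rejects, no caliper | Rejects, caliper |
|---|---|---|---|---|---|---|
| 105,471, 30% | 60% | moderate | 0.472 → 0.471 | 1.204 → 1.208 | 100% | 0% |
| 105,471, 30% | 50% | moderate | 0.472 → 0.463 | 1.206 → 1.204 | 100% | 5% |
| 105,471, 30% | 50% | weak | 0.245 → 0.234 | 1.043 → 1.041 | 95% | 5% |
| 105,471, 30% | 40% | moderate | 0.471 → 0.094 | 1.206 → 1.044 | 100% | 0% |
| 105,471, 30% | 40% | weak | 0.246 → 0.007 | 1.047 → 1.003 | 0% | 0% |
| 105,471, 30% | 26% | moderate | 0.477 → 0.004 | 1.218 → 1.004 | 15% | 10% |
| 200,000, 3% | 50% | moderate | 0.471 → 0.464 | 1.214 → 1.211 | 100% | 0% |
| 200,000, 3% | 50% | weak | 0.246 → 0.240 | 1.032 → 1.031 | 33% | 20% |
| 2,227, 50% | 50% | moderate | 0.473 → 0.419 | 1.202 → 1.180 | 78% | 3% |
| 2,227, 50% | 50% | weak | 0.253 → 0.211 | 1.046 → 1.040 | 10% | 5% |
| 20,686, 30% | 25% | strong | 0.853 → 0.094 | 1.441 → 1.047 | 30% | 8% |
| 20,686, 30% | 10% | strong | 0.912 → 0.005 | 1.506 → 0.993 | 7% | 7% |

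At N = 20,686 and 50:50, rejection was 35% with weak confounding, 92% with log-odds 0.5 and outcome HR 1.2, and 100% with moderate confounding. Scenarios had 15 to 200 replicates, so rates are approximate; the 20% with a caliper rests on 15.

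For hypertension subclasses, small separate runs with rare events agree in direction. With 5% events and a crude HR of about 1.22, matched HRs were 1.003, 1.034 and 1.161 at 26%, 36% and 48% exposed, with rejection of 0%, 65% and 100%. With 3% events and N = 363,397, rejection was 0% to 13% at 26%, 0% to 25% at 36% and 20% to 90% at 41%.

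**The case against.** A reader might infer that the matched analysis would reject a true null almost always. The documents do not support that. They give neither group ratios nor strength of confounding, and the simulated rate runs from nominal to 100%. Nor can exposed shares derived for hypertension in cohort B be combined with the sample sizes and high death rates of cohort C. A reader might also take 26% as a floor for every hypertension pair. But 93,589 is a mean, single subclasses may be far smaller, and the Exposures section puts patients who start several drugs into separate combination groups. These points stand.

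The article is condensed, and caliper width and balance diagnostics are often left to an analysis plan. That stands only in part. The section does not stay silent on restriction: it names a trimming rule and defines it, and that rule does not limit match distance.

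The Covariates section also mentions matching on date of birth, sex, index year and length of record. Its wording is unclear, it is not tied to the propensity step, and the simulation ignores it. If applied, it would remove imbalance on those variables only.

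Finally, all four methods will be reported, and the fully adjusted Cox model does not use the matching. This limits the harm but does not make the matched HR informative where groups are near equal.

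**Conclusion.** The point holds for comparisons in which the groups are near equal or the exposed outnumber the comparators. There the rule as written does not produce the balanced sample it promises. At 50:50, 99.6% to 100% of the smaller group is matched and the matched HR stays close to the crude one. Under assumed moderate to strong measured confounding and about 20,000 patients or more, a true null is rejected in roughly 90% to 100% of replicates.

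With weak confounding, rare events, the ALS sample size or exposed shares of about 25% or less, rejection is generally lower and often near nominal. There are exceptions at the edges: 95% with weak confounding at 50:50 and N = 105,471, and 30% with strong confounding at 25% exposed.

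Even at 40% exposed, the moderate case leaves a matched HR of 1.044. Table 3 counts an HR of 0.968 (1/0.968 = 1.033) as detectable, so the leftover bias can be as large as the effects sought.

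The adjusted Cox analysis is unaffected. The rule should be corrected before the matched results are used to judge the other methods, but it does not invalidate the study.

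**What to change.** In Propensity matched regression, match on the logit of the propensity score within a stated caliper (for example 0.2 SD of the logit), and leave patients with no comparator inside it unmatched. For each comparison, report the group sizes, the number unmatched and the standardised mean difference of every covariate after matching. Adjust the matched Cox and logistic models for residual imbalance. Where groups are near equal in size, propensity weighting on the full sample is an alternative.

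This takes a few sentences and no new data. The cost is that some patients are dropped: at 50:50 in the simulations, 66% to 91% of the smaller group was still matched. The residual SMD was then 0.003 to 0.010 and the HR 0.99 to 1.01. The estimate then applies to patients who can be matched, and the report should say so.

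### In cohort B, fixed 1:1 propensity matching gives less power than the unmatched Cox comparison sized in Table 3, most clearly for hypercholesterolaemia (about 51% against a nominal 80%)

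*Protocol article*

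**What the plan says.** The Study size section presents "minimum sample size and detectable HR (α=0.05, β=0.80) for the Cox regression analysis of cohorts B and C". It defines the effect size thus: "The minimum detectable HR is taken to be the detectable HR for the smallest exposed group tested against the control group". The sample is defined in the same place: "The minimum sample size is the sum of patients in the smallest exposed group and the control group". The tabulated HRs are therefore for an unmatched comparison that uses every control.

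The cohort B rows of Table 3 (total, minimum sample size, minimum detectable HR) are:

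- "Treatment for hypercholesterolaemia 808 687 788 479 0.844"
- "Treatment for type 2 diabetes 200 800 158 775 0.943"
- "Treatment for hypertension 1 018 519 269 808 0.968"

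The Cohort B section makes the most commonly prescribed subclass the control. Box 1 lists 10 subclasses for hypertension, 6 for hypercholesterolaemia and 3 for type 2 diabetes, each count including the control.

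The Propensity matched regression section pairs patients "with the closest propensity score on a ratio of 1:1 using a nearest neighbour algorithm with no replacement", within the region of common support, and estimates HRs by Cox regression in the matched sample. The article gives no power or detectable HR for that sample. The Study size section nevertheless concludes that "our statistical power will be more than adequate to test all of our proposed hypotheses", and adds that this holds under Bonferroni correction.

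**The concern.** Making the commonest subclass the control builds imbalance into cohort B. A 1:1 ratio without replacement reduces the control arm to the size of the exposed arm, so the matched Cox model has less information than the comparison sized in Table 3.

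The Confounding and Statistical methods sections plan to examine the methods side by side, look for signs of uncontrolled confounding, and weigh discrepancies on the merits of each method. If one method is markedly less precise by design, some disagreement will reflect imprecision alone. The unused controls are already in the dataset.

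**Working it through.** **Inputs.** Table 3 and Box 1 as above; alpha 0.05, taken as two-sided; the stated β=0.80 read as 80% power.

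**The plan's own figures.** The Schoenfeld relation is N·ψ·p(1−p) = (1.960+0.842)²/ln(HR)², where p is the exposed share and ψ the event probability. Neither is in the article (subclass counts are in supplementary files not shown), so the tabulated HRs cannot be reproduced. Only ψ·p(1−p) can be recovered: 0.0275 for hypertension, 0.000346 for hypercholesterolaemia and 0.01435 for type 2 diabetes. The nominal 80% is taken as stated.

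**Effect of matching.** This does not need ψ if event rates are similar in matched and unmatched patients. The unmatched information is N·ψ·p(1−p). With every exposed patient matched 1:1 there are 2pN patients, and the information is 2pN·ψ·¼. Then:

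- information ratio = 0.5/(1−p)
- power at the tabulated HR = Φ(2.802·√ratio − 1.960)
- detectable HR after matching = HR^(1/√ratio)

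**Upper bound on p.** Patients outside the tabulated comparison belong to the remaining non-control subclasses, each at least as large as the smallest. So the smallest is at most (total − minimum sample)/(subclasses − 2).

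| | Hypercholesterolaemia | Type 2 diabetes | Hypertension |
|---|---|---|---|
| Total − minimum sample | 808 687 − 788 479 = 20 208 | 200 800 − 158 775 = 42 025 | 1 018 519 − 269 808 = 748 711 |
| Divided by | 4 | 1 | 8 |
| Smallest subclass at most | 5052 | 42 025 | 93 589 |
| Controls at least | 783 427 | 116 750 | 176 219 |
| Controls per exposed, at least | 155 | 2.8 | 1.9 |
| Controls discarded, at least | 99% | 64% | 47% |
| p at most | 0.0064 | 0.265 | 0.347 |
| Information ratio at most | 0.503 | 0.680 | 0.766 |
| Power at most | 51.1% | 63.7% | 68.8% |

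**Lower bound on p.** Since ψ cannot exceed 1, the recovered products give p of at least 0.0003, 0.015 and 0.028 in the same column order.

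| | Power after 1:1 matching | Detectable HR after matching | Table 3 HR |
|---|---|---|---|
| Hypercholesterolaemia | 50.9–51.1% | about 0.787 | 0.844 |
| Type 2 diabetes | 51.4–63.7% | 0.921–0.931 | 0.943 |
| Hypertension | 52.0–68.8% | 0.956–0.964 | 0.968 |

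**More controls per exposed patient.** With k controls each, the information ratio is [k/(k+1)]/(1−p). For hypercholesterolaemia, 1−p = 783 427/788 479 = 0.9936. At k = 4 the ratio is 0.800/0.9936 = 0.805 and power is 71%. At k = 10 it is 0.909/0.9936 = 0.915 and power is 76%.

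**Sensitivity.** A one-sided alpha of 0.05 would change the three upper bounds on power to about 55%, 66% and 70%.

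**The case against.** The best defence is that 1:1 nearest-neighbour matching is a legitimate trade of variance for bias. In a very large database where confounding is the main worry, taking the closest match is defensible. That stands as to validity: the point here concerns efficiency only. It carries little weight where there are at least 155 controls per exposed patient. It carries more for diabetes and hypertension, where at the bounds only about 2.8 and 1.9 controls are available and the detectable HR moves only from 0.943 to 0.931 and from 0.968 to 0.964.

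It is also fair to say that any less precise analysis has under 80% power at another analysis's detectable HR, that the protocol never names these HRs as target effects, and that Table 3 shows minimum cases, so larger subclasses do better.

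A reader might infer more than the article supports:

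- *That Table 3 is misstated.* It is not. Text and title both tie it to Cox regression, and the sample is defined openly.
- *That the loss runs through all of Table 3.* Cohort C compares treated with untreated patients and its exposed share is not given. Matched power there could lie anywhere from about 51% to 80%.
- *That 51%, 64% and 69% are the powers of particular comparisons.* They are ceilings, one per cohort B row. The hypertension ceiling needs all nine non-control subclasses to be equal in size.
- *That most controls are always discarded.* At the hypertension bound the share is 47%.
- *That information is halved throughout.* This is firm only for hypercholesterolaemia. The limit of a vanishingly small exposed group would give detectable HRs of 0.920 (diabetes) and 0.955 (hypertension), both just outside what Table 3 allows.
- *That loss of significance would be taken as proof of confounding.* The article sets no such rule. It commits to presenting all findings and judging each method in context.

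**Conclusion.** The point holds for cohort B. Fixed 1:1 matching gives the propensity analysis less power than the comparison sized in Table 3. The loss is material for hypercholesterolaemia, where the bounds nearly coincide. For diabetes and hypertension the size of the loss depends on subclass counts not shown here, and it may be small in HR terms.

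The result assumes non-overlapping subclasses (the Exposures section does describe combination groups), similar event rates in matched and unmatched patients, two-sided alpha and a match for every exposed patient. Losses to common support would lower power further. The starting 80% cannot be verified from the article.

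The wording at fault is the Study size claim that power suffices for every proposed hypothesis. The article supports it with unmatched Cox figures only, not for the matched analysis.

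**What to change.** In Propensity matched regression, where controls greatly outnumber the exposed subclass (chiefly hypercholesterolaemia), replace the fixed ratio with variable-ratio matching within a stated caliper of the propensity score, for example up to 4 to 10 controls per exposed patient. Analyse with matching weights or stratified by matched set, and keep 1:1 as a sensitivity analysis. For diabetes and hypertension a high maximum ratio may add little, and the subclass counts should decide.

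In Study size, limit the adequacy statement to the unmatched Cox analysis and give the matched-sample detectable HRs beside Table 3.

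The cost is protocol wording and some computing, with no new data. The downside is slightly less close matches for the additional controls, limited by the caliper and visible in a check of covariate balance.
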